## DESCRIPTION OF STUDY

Please address each section carefully and in detail. Failure to do so will delay the review of your study.

### PURPOSE AND PROCEDURES:

1. Describe the study format and whether it is single or multi-center; industry-sponsored or investigator initiated; and the funding source.

This is a multi-center, investigator-initiated study examining the variation between individuals in blood lipid metabolites, cytokines, gene expression, metabolomic fingerprint, and blood and urine eicosanoid levels, and the changes in these levels in response to omega-3 fatty acid (w3FA) supplementation in patients with immunoglobulin A nephropathy (IgAN) compared with healthy controls. The funding source is a pilot grant from the Center for Human Nutrition Research (CHNR).

2. Briefly describe the specific aims of the study, research methods and procedures.

It is unclear to what extent blood lipid levels, cytokines, gene expression, metabolomic fingerprint, and blood and urine eicosanoid levels vary between individuals, and it is also unclear how they change in response to short-term w3FA or fish oil supplementation. It is necessary to establish the means and standard deviations in the levels of these metabolites in the healthy population, in order to better understand the mechanisms related to lipid metabolism of metabolic diseases that are modified by w3FA. Specifically, the project will examine the differences between healthy controls and patients with immunoglobulin A nephropathy (IgAN) before and after w3FA supplementation. The IgAN patient samples will be obtained from collaborators from a previously completed project. These samples have been stored in a freezer and are awaiting analysis. The portion of the project involving the healthy controls remains to be carried out.

This project will resolve the following **specific aims**:

- Establish preliminary estimates of means and standard deviations in the levels of w3FA within different lipid classes in the blood, the levels of inflammatory cytokines, gene expression, metabolomic fingerprint, and the extent of variation between healthy individuals compared with IgAN patients in these variables before and after w3FA/fish oil supplementation.
- Determine preliminary estimates of means and standard deviations in the levels of eicosanoids in the blood and urine of healthy individuals compared with IgAN patients before and after w3FA/fish oil supplementation.
- Develop methods and preparative protocols for the analysis of w3FA-derived eicosanoid metabolites in the blood and urine using samples from healthy individuals and IgAN patients.

The **research methods and procedures** that will be used for this study involve the following:

- ~~Thirty healthy volunteers willing and able to take 6 g of fish oil for 6 weeks will be recruited from the general UC-Davis population including students, faculty, and staff. The volunteers will be recruited by personal communication at seminars and other school-related activities as well as flyers that will be posted on campus.~~
- ~~The volunteers will be contacted and a mutually agreed-upon date will be scheduled for a brief meeting during which time subjects will receive a copy of the consent form to read over, as well as the first morning urine collection tube. This will be followed by a mutually agreed-upon date for~~

~~scheduled for a brief meeting during which time subjects will receive a copy of the consent form to read over, as well as the first morning urine collection tube. This will be followed by a mutually agreed-upon date for the first blood draw and urine collection. The researcher will contact the volunteer the day before the first scheduled study date to confirm and remind the volunteer about fasting, about collecting the first morning urine void, and the time and location of the study.~~

- The participants will come to the Ragle Human Nutrition Center ([name]) between 7 and 9 am after an overnight fast, at which point they will be weighed (clothed but with no shoes) on a digital scale, as well as sign a consent form and discuss all their rights regarding the study. A registered phlebotomist will take 20 mL of blood by venipuncture for their pre-supplementation blood draw. Volunteers will turn in their first morning urine sample at this time.
- Immediately after blood collection, the researcher will separate the red blood cells and peripheral blood mononuclear cells (PBMC) from the plasma, aliquot the samples, and then store them in a -70°C freezer for future molecular and genetic analyses.
- Lipid analysis will be performed at Lipomics Technologies Inc. in West Sacramento, using published methods for quantitative lipid analysis (1). Briefly, lipids will be extracted with chloroform/methanol, followed by derivatization with methanolic HCl, separation of lipid classes with liquid chromatography, and finally fatty acid identification and quantitation with gas chromatography.
- Eicosanoid analyses will be performed in the [name] Lab using published methods for quantitative eicosanoid analysis (2).
- Untargeted metabolites in the mass range of 100 – 1600 will be analyzed by liquid chromatography coupled to mass spectrometry in the [name] Lab according to published methods for global metabolomic fingerprinting (3).
- One aliquot of PBMC will be stored for future gene expression analysis and DNA will be isolated from a second aliquot and quantified using Qiagen DNA isolation and Picogreen quantitation kits, respectively, according to the manufacturer's instructions. Gene expression and genotyping analyses will be performed using Taqman-based assays (4).
- Cytokine analyses will be performed using multiplexed cytokine analysis as previously described (5).
- Data analysis will be performed using standard statistical techniques using JMP software and specialized bioinformatic tools developed at Lipomics for lipidomic data analysis using specially developed software.

3. Address if therapeutically removed tissue will be collected, what types, and for what purposes.

No **tissues** will be removed for these analyses.

4. Specify the nature, frequency and duration of tests, if any.

The blood draws and urine collections will be performed once before and once after 6 weeks of supplementation with fish oil. The volunteers will come in on three occasions to the Ragle Center. On the first visit, the volunteers will meet with the researcher to go over the consent form, make an appointment for their blood draw visits, and obtain their first morning urine collection equipment as well as instructions on how to use it. On the scheduled first blood draw visit, they will have a fasting blood draw taken first thing in the morning, and at the same time bring in their first morning urine sample and obtain their 6 weeks of fish oil capsules. After 6 weeks the volunteers will return for the post blood draw visit, on which occasion they will again bring in a first morning urine sample and have a fasting blood draw taken. These 3 occasions are the only times the volunteers will need to come to the Center. They will take the capsules each day at their convenience at home/work.

sample and have a fasting blood draw taken. These 3 occasions are the only times the volunteers will need to come to the Center. They will take the capsules each day at their convenience at home/work.

5. If blood samples will be collected, identify in what manner and the maximum amount that will be collected over any 6 week period (if subjects are co-enrolled in other research studies, the volume of blood from the other study should also be included):

☒ venipuncture   ☐ venous catheter   ☐ arterial puncture   ☐ arterial catheter  
☐ cutaneous

The blood samples will be collected by **venipuncture**, and the **maximum amount** that will be collected at each session is 100 mL, and over 6 weeks is 200 mL.

6. Any additional procedures (noninvasive) involved in this study activity must be described.

There will be no **additional procedures** involved in this study.

7. If the study involves incomplete disclosure, provide the rationale.

There will be no **incomplete disclosure** involved in this study. Volunteers will be fully informed of the analyses that will be performed with their samples, of the aims of the study, and of all the procedures that will be performed during the study.

8. If this activity will be utilizing existing data, specify the source and how the data will be retrieved, reviewed, coded and stored.

Existing data and samples will be collected from our collaborator for the IgAN patients. The samples are currently being shipped to us from our collaborator. The samples and data will arrive with no identifiers and will be coded with a randomly-generated ID number corresponding to each volunteer.

There will be no existing data collected from the healthy control volunteers. They will only be asked to fill out a brief questionnaire for their age, gender, whether they are pregnant, whether they are currently using any medications and if so which ones, and whether they consider themselves to be healthy. The volunteers will also be weighed on a digital scale clothed but without shoes. They will provide 2 fasting blood samples and 2 first morning urine samples, once before and 6 weeks after supplementation with fish oil. All data will be recorded in a digital file (Excel worksheet), which will be backed up on a disc.

Each volunteer will be identified by a random, computer-generated 5-digit number. The file will be stored without any identifiers (the subjects' names or contact information will not be recorded) on the [name] lab backup server. Contact information for the volunteers, so that a reminder e-mail or phone call can be made, will be kept in a logbook separate from the digital file containing volunteer information, and will not be traceable to the samples or to the file.

9. Address the location and duration of the study including follow-up period.

Volunteers will come to the Ragle Human Nutrition Center at [name] on the UC Davis campus, and they will be there for about 40 minutes in the morning between 7 and 9 am once before and then again 6 weeks after supplementation with fish oil on the blood draw days, as well as for a brief 15 minute meeting prior to the blood draw visits.

10. Clarify how you plan to monitor data to ensure subject safety.

Only healthy, adult, non-pregnant volunteers weighing at least 110 pounds will be recruited for this study. Only limited medical history and other personal information will be collected from volunteers to determine their health status. Specifically, the volunteers will be asked some questions to ascertain whether they are healthy and fit to go through the study protocol with no danger to their health and welfare. The questions are: 1) whether they are currently using any prescription or non-prescription medications, and if so which ones; 2) whether they have been diagnosed by their physician with a disease, and if so which one(s); 3) whether they currently have any form of

health and welfare. The questions are: 1) whether they are currently using any prescription or non-prescription medications, and if so which ones; 2) whether they have been diagnosed by their physician with a disease, and if so which one(s); 3) whether they currently have any form of anemia; 4) whether they have any other health conditions or concerns that might preclude them from participating in this study, and if so to list these; and 5) whether they have been ill with a cold or flu or had a major injury in the last 2-4 weeks. Subjects will be excluded if they have been diagnosed with a disease, if they are pregnant or nursing or if they suspect they might be pregnant, if they have some form of anemia or are not sure whether they have anemia, if they had an illness, infection, or injury within the last 2-4 weeks, and if they are taking any blood thinners or other anticoagulants. Volunteers will also be excluded if they are taking medications that alter lipid metabolism such as statins (HMG CoA reductase inhibitors), any kind of steroids, and PPAR agonists. However, we do not expect to encounter individuals who have not been diagnosed with a disease but who are taking any such medications. Volunteers will be excluded if they are taking over-the-counter allergy medication and NSAIDs, however, if they are willing to discontinue these for the period of the study they will not be excluded. In the unlikely event that the fish oil supplement causes side effects volunteers will be instructed to contact their doctor immediately, and also to contact the investigators by phone, or e-mail as soon as possible. No other data monitoring is planned for this study.

11. Address whether you have the appropriate resources (study personnel and facilities) to conduct this study.

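### The only signature the protocol describes is at the baseline blood-draw visit, after the volunteer has fasted overnight and collected the first morning urine for the study

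*Protocol*

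**What the plan says.** The relevant text is in the Protocol, Purpose and Procedures, items 2 and 4.

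- **Item 2 (research methods), baseline draw visit.** Participants come to the centre "between 7 and 9 am after an overnight fast". The signature is placed at this same visit, together with the weighing: "at which point they will be weighed (clothed but with no shoes) on a digital scale, as well as sign a consent form". The discussion of their rights is tied to the signing: "as well as sign a consent form and discuss all their rights regarding the study". The visit is identified as the baseline one: "A registered phlebotomist will take 20 mL of blood by venipuncture for their pre-supplementation blood draw". The urine is received at the same visit: "Volunteers will turn in their first morning urine sample at this time".
- **Item 4 (nature and frequency of tests), first visit.** "On the first visit, the volunteers will meet with the researcher to go over the consent form, make an appointment for their blood draw visits". At this visit they also "obtain their first morning urine collection equipment as well as instructions on how to use it".
- **Item 9 (location and duration).** The first visit is a meeting of about 15 minutes before the blood-draw visits. Signing is not mentioned.
- **Waiver of Informed Consent.** Answered as not applicable.

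**The concern.** Written consent normally comes before anything a volunteer does solely for the study. Here the protocol states the order of events, and that order puts two such steps ahead of the signature: the overnight fast and the collection of the first morning void. Because the order is written into the plan, it applies to every healthy volunteer and not to an occasional case.

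What is at stake is mainly participant protection and a clean consent record. The statistical interest is secondary. The baseline urine is the before-supplementation half of the urine eicosanoid comparison in the second specific aim, so it is sensible to keep its consent status beyond question. The protocol seeks no waiver that would cover collection ahead of a signature.

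**Working it through.** No formula applies, and the plan gives no figure to reproduce. The check is to put the passages in time order.

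1. **First visit (item 4; about 15 minutes, item 9).** The form is gone over with the researcher, appointments are made, and the urine equipment and instructions are handed out. No signature is stated.
2. **Evening and morning before the draw (implied by item 2).** Arrival is between 7 and 9 am after an overnight fast, so the fast is complete on arrival. A first morning void that is handed in at that visit, using equipment issued earlier, must have been collected before arrival. That it is collected at home is an inference. That it is collected before the visit is not.
3. **Baseline draw visit (item 2).** Weighing, signature and rights discussion, venipuncture, and hand-over of the urine.

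Both parts of step 2 come before the only signature in the text, which is in step 3.

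I then looked for any statement that would move the signature earlier.

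- Item 4 speaks of going over the form, not of signing it.
- Item 9 mentions the short meeting without a signature.
- The struck-through text in item 2 says only that volunteers receive the form to read. It is deleted text and serves as context only.
- The waiver section requests nothing.

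None of these places a signature before the fast or the urine collection.

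**Extent.** Subject Selection, item 1, plans 30 healthy volunteers. Purpose and Procedures, item 8, gives each of them two urine samples, so 30 × 2 = 60 control urine samples. The 30 baseline samples are self-collected before the signature. The 30 samples taken after supplementation are not affected.

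**The case against.** The strongest reply is that volunteers are not kept in the dark. They go over the form with the researcher at the meeting where they receive the urine kit, and item 7 of the same section commits to informing them fully about aims, procedures and analyses. The study receives the urine only at the visit where the form is signed, so a volunteer who declines need not hand anything over. No passage has the study holding or analysing a sample before the signature. What precedes the signature carries little burden: no blood is drawn and no supplement is taken. The interval between reading and signing can also be seen as time to reflect. All of this stands, and it limits the point to when consent is documented and rights are discussed.

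It may also be said that going over the form at the first visit was meant to include signing, or that the consent pages, which are not in the file, settle the timing. Item 4 does not say so, and item 2 expressly puts signing at the draw visit. If signing at the first visit was intended, items 2 and 4 conflict and need the same correction.

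A reader might infer more than the documents support:

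- **That weighing precedes consent.** Item 2 joins weighing and signing without ordering them.
- **That eligibility questions are asked before consent, or too late.** The protocol does not say at which visit they are asked, so either reading is conjecture.
- **That other restrictions begin before consent.** The seafood and seaweed restriction is tied to the 6 weeks of supplementation. The stopping of NSAIDs and allergy medication is stated for 6 weeks or for the study period. Apart from the overnight fast, no pre-baseline restriction is described.
- **That the order amounts to a protocol deviation in every volunteer.** Following the protocol as written is not a deviation from it.

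**Conclusion.** The point holds as a matter of sequence. As written, written consent and the rights discussion come after a study-specific fast and a self-collected urine sample in all 30 healthy volunteers. This is a defect in the timing of documented consent. It does not show that volunteers are uninformed.

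It would be tempting to conclude that all 30 baseline urine samples, and with them every paired urine change in the controls, are lost. The documents do not support that. It would require an ethics board to bar the samples, and nothing in the text says it would. The protocol is itself written on a form for ethics review, so the sequence is open to question before any sample exists. Loss of these data is a possibility only. No sample size, power or error rate depends on this point.

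The conclusion rests on the protocol text shown, without the consent pages, and on reading item 4 as it stands, with no signature at the first visit. Confidence is high for the sequence and does not extend to any consequence for the data. The change is worth making because it protects participants at very little cost.

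**What to change.** Reconcile items 2 and 4 of Purpose and Procedures so that one place states when consent is signed.

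- **Item 4, first visit:** state that the researcher goes over the form, discusses the volunteer's rights and obtains the signature, and only then hands out the urine kit and gives the fasting instructions.
- **Item 2, baseline draw visit:** remove the signing and rights discussion, and replace them with a brief verbal reconfirmation of consent before the visit's procedures begin.

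The cost is a wording change in two places and a few extra minutes at the existing 15-minute meeting (adjust the duration in item 9 if needed). No visit, procedure or sample is added.

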### SUBJECT SELECTION:

1. Identify the subject population.

The **subject population** will consist of 30 healthy non-pregnant adults 18-65 years of age, weighing at least 110 pounds. The subjects will be individuals who have not been diagnosed with any disease, who are not taking any prescription medications that affect lipid metabolism or that are anticoagulants/blood thinners, who do not have any form of anemia, and who have not had any illness, infection, or injury on the last 2-4 weeks.

2. Address how subjects will be recruited: \_\_\_direct person to person solicitation, \_\_\_by telephone, \_\_\_letter, \_\_\_advertisement, \_\_\_press release, \_\_\_notices, \_\_\_other.  
Provide the text.

The **subjects will be recruited** with flyers posted around the UC Davis campus. The subjects will include students, faculty, and staff. The subjects will be told the following:

"We are looking for volunteers to participate in a fish oil supplementation study. You will need to come in once before the supplementation for a blood draw and a first morning urine collection. You will take 6 g of fish oil every day for 6 weeks, and not eat any seafood, or seaweed during that time. Then you will come back for another blood draw and first morning urine collection. You would need to be a healthy adult between the ages of 18 and 65, weigh at least 110 pounds, not be taking any medications, not pregnant, and not diagnosed with any diseases in order to participate in the study. If you qualify, would you be interested in participating in this study?"

3. State from where subjects will be recruited, when and how many.

**The subjects will be recruited from the general population of the UC Davis campus, and will include students, faculty, and staff. Thirty volunteers will be recruited over a 6-month period between March and August of 2008.**

4. Specify the age of the research subjects.

The subjects' **age** will be between 18 and 65 years old.

5. List all criteria for including and excluding subjects.

#### a. Inclusion criteria:

- i. Weight at least 110 pounds
- ii. Adult (aged 18-65 years old)
- iii. Disclose which medications currently taking
- iiii. Able to come to the Ragle Center at the designated times
- v. Able to give blood
- vi. Able to take 6 g fish oil per day for 6 weeks
- vii. Able to carry out first morning urine collection

- collection
  - vii. Able to carry out first morning urine
  - viii. Able to stop or avoid taking NSAIDS and allergy medications for 6 weeks
  - ix. Able to stop or avoid eating seafood and seaweed for 6 weeks
- b. Exclusion criteria:
  - i. Pregnant or nursing (or unsure if pregnant)
  - ii. Diagnosed with a disease by their physician
  - iii. Currently taking prescription medications that alter lipid metabolism (such as HMG CoA reductase inhibitors, PPAR agonists, steroids) and/or anti-coagulants
  - iiii. Currently has some form of anemia (or unsure)
  - v. Has an existing health condition or concern
  - vi. Unable to stop or avoid taking NSAIDS and allergy medications for 6 weeks
  - vii. Unable to stop or avoid eating seafood or seaweed for 6 weeks
  - viii. Unable to give blood or do first morning urine collection
  - ix. Recently recovering from a major injury, infection, or illness (in the last 2-4 weeks)

6. If women and minorities are excluded, provide rationale for such exclusion.

Women and minorities will not be excluded from this study.

7. Attach the translated documents for subjects whose primary language is not English.

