**COSTS/COMPENSATION TO SUBJECTS:**

1. If the study involves the possibility of added expenses to the subject or to a third party, such as an insurer (e.g., longer hospitalization, extra laboratory tests, travel) address the magnitude of those expenses and how this is justified.

There are **no added expenses** to the subject or to any third party associated with this study.

2. Describe the amount and type of compensation that will be paid to subjects and how that compensation will be staged/pro-rated.

The **compensation** to the subjects will be 6 weeks of free fish oil supplements.

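### Outside omega-3 is restricted only from seafood and seaweed; no criterion, screening question or instruction names omega-3 supplements, so current users can enter and can add to the study dose

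*Protocol*

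**What the plan says.** **Eligibility (Protocol, SUBJECT SELECTION, item 5).** The only criteria on outside omega-3 concern food. Volunteers must be "Able to stop or avoid eating seafood and seaweed for 6 weeks", and the matching exclusion is "Unable to stop or avoid eating seafood or seaweed for 6 weeks". The drug criteria cover prescription lipid-altering drugs, anticoagulants, and NSAIDs or allergy medications that the volunteer cannot stop. Fish oil, omega-3 products and dietary supplements in general appear nowhere in either list.

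**Timing (SUBJECT SELECTION, item 2).** The flyer says: "You will take 6 g of fish oil every day for 6 weeks, and not eat any seafood, or seaweed during that time". No restriction of any kind precedes the first draw.

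**Screening (PURPOSE AND PROCEDURES, items 8 and 10).** Item 8 describes the questionnaire: "They will only be asked to fill out a brief questionnaire for their age, gender, whether they are pregnant", followed by medications and self-rated health. Item 10 asks "whether they are currently using any prescription or non-prescription medications, and if so which ones", and then about disease, anemia, other conditions and recent illness. Neither list names supplements.

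**Conduct (PURPOSE AND PROCEDURES, item 4).** Capsules are taken at home or work. Nothing is said about the volunteer's own omega-3 products.

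**Purpose (PURPOSE AND PROCEDURES, item 2).** The first aim is to "Establish preliminary estimates of means and standard deviations in the levels of w3FA within different lipid classes in the blood", together with other markers, before and after supplementation, in healthy people compared with IgAN patients.

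**The concern.** The food restriction shows that the protocol means to control omega-3 from outside the study, yet it leaves open the most direct source. RISKS, item 1, describes the study product as obtainable over the counter and likens the daily dose (6 g fish oil, 3.5 g omega-3) to a 9-ounce salmon fillet. The fillet is barred during the six weeks; a capsule of the same oil is not.

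Two separate effects follow if users enter:

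- **At the first draw.** A current user has already been supplemented, so the sample is not a pre-supplementation one and the change to week 6 is likely to be smaller.
- **During the six weeks.** A volunteer who takes personal capsules as well receives more than the study dose, and the second draw reflects an intake that nobody recorded.

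Means, SDs and their before-after behaviour are what this pilot sets out to deliver. Since the exposure is not specifically asked about, a later analysis plan could not reliably adjust for it or run a sensitivity analysis on it.

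**Working it through.** The protocol states no figure that rests on this point, so there is nothing to reproduce. The check is a reading of the text followed by a sense of scale.

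**1. Text check**

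| Source of outside omega-3 | Restricted before first draw? | Restricted during the 6 weeks? | Named in screening? |
|---|---|---|---|
| Seafood, seaweed | No | Yes | Only as ability to avoid |
| Over-the-counter fish oil or other omega-3 | No | No | No |

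**2. Chance that at least one user enters.** The number of controls comes from the protocol, whose sample "will consist of 30 healthy non-pregnant adults 18-65 years of age". The share of users, q, is an assumption. P(at least one) = 1 − (1 − q)^30:

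- q = 2%: 45% (expected 0.6 users)
- q = 5%: 79% (1.5)
- q = 10%: 96% (3)
- q = 20%: 99.9% (6)

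**3. Effect on the baseline.** Suppose users sit d within-group SDs above non-users, with d from 1 to 3 (assumed). The mean shifts by q·d, and the SD is multiplied by √(1 + q(1 − q)d²):

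- q = 5%: shift 0.05 to 0.15 SD; SD factor 1.02 to 1.20
- q = 10%: shift 0.10 to 0.30 SD; SD factor 1.04 to 1.35
- q = 20%: shift 0.20 to 0.60 SD; SD factor 1.08 to 1.56

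**4. Effect on the change.** Assume a non-user change of mean 1 and SD 0.4, and a user mean change u of 0.3 to 0.7 with the same within-group SD. Then:

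- mean = (1 − q) + q·u
- SD = √(0.4² + q(1 − q)(1 − u)²)
- n for a later test of mean change is proportional to (SD/mean)², so the ratio to the non-user n is (SD/mean)² / 0.4²

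| q | u | Mean | SD | n ratio |
|---|---|---|---|---|
| 5% | 0.7 | 0.985 | 0.405 | 1.06 |
| 5% | 0.3 | 0.965 | 0.428 | 1.23 |
| 10% | 0.7 | 0.970 | 0.410 | 1.12 |
| 10% | 0.3 | 0.930 | 0.452 | 1.47 |
| 20% | 0.7 | 0.940 | 0.418 | 1.23 |
| 20% | 0.3 | 0.860 | 0.488 | 2.01 |

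Worked line for q = 10%, u = 0.3: mean = 0.9 + 0.03 = 0.93; variance = 0.16 + 0.09 × 0.49 = 0.2041; ratio = (0.2041 / 0.8649) / 0.16 = 1.47.

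The model covers only a smaller response in existing users. It does not cover extra capsules taken during the study.

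**The case against.** **Some users may be caught.** The item 10 question includes non-prescription medications, inclusion criterion iii requires medications to be disclosed, and the flyer asks for people who take none. The protocol itself blurs supplement and drug, since it calls prescription Omacor a supplement. So it would be too strong to say that use is never asked about. This part stands. What remains is that supplements are not named, and that no criterion excludes, or requires stopping, when an over-the-counter omega-3 product is reported.

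**Users may belong in the baseline.** The protocol speaks of levels in the healthy population and of variation between individuals. If the first draw is meant to describe habitual intake, users are part of natural variation, and regular fish eaters enter that draw without any washout too. This also stands in part: a reader might infer that the healthy baseline is simply biased upward, but that depends on which baseline is wanted. The argument does not excuse uncontrolled intake during the six weeks, when the protocol already bars dietary sources.

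**Self-selection is not shown.** Compensation "will be 6 weeks of free fish oil supplements", and a reader might infer that this draws in existing users. The flyer text does not mention free capsules, and the protocol offers no evidence of over-representation.

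**The IgAN contrast could move either way.** The patient samples come from a completed project whose supplement rules are not described. If those patients were not screened, excluding users among controls alone could itself create a difference between the groups.

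**It is a pilot.** The estimates are called preliminary and no decision rule fails. That bears on severity. The consent form is not available here and might carry an instruction, but the protocol's own list of all criteria does not.

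**Conclusion.** The gap is real and should be fixed. As written, current omega-3 users can enter, their first draw is then not a true pre-supplementation sample, and any volunteer can exceed the study dose without its being recorded. The mean and SD of the change can be distorted; the effect on the comparison with IgAN patients depends on how those samples were screened.

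The size rests wholly on assumptions: with 5% to 20% users and a user change of 0.3 to 0.7 of the non-user change, the n ratio for a later study runs from about 1.06 to 2.0. The protocol names no such study, so this gauges how far the pilot's estimates could mislead and is not an error in a stated figure.

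A reader might infer that users will certainly be in the sample, or that the estimates are unusable. The document supports neither: it gives no prevalence of use, and at 5% users the ratio is only 1.06 to 1.23. The point is a cheap improvement to a pilot, best made before enrolment because exposure that was not recorded cannot be reliably recovered afterwards.

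**What to change.** 1. In SUBJECT SELECTION, item 5, add an exclusion for use of fish oil or any other omega-3 supplement within a period before the baseline draw, the period to be set by the investigator.
2. Extend the existing 6-week seafood and seaweed restriction to non-study omega-3 products.
3. In PURPOSE AND PROCEDURES, item 10, name dietary supplements, including omega-3 products, in the medication question. Ask again at the post-supplementation draw and record the answers.
4. Add a matching line to the flyer in SUBJECT SELECTION, item 2.
5. State what is known about supplement use in the IgAN project, so that the group comparison can be read accordingly.

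The cost is one criterion, a wider restriction, one question asked twice, a flyer line and a sentence on the patient samples. The downside is a few volunteers turned away. The change does not deal with habitual seafood intake before the first draw, which stays part of the baseline.
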